### **1.1 Rationale for the execution of the study**

Cardiovascular disease is a great burden in the context of public health, as well as the low pharmacological compliance of patients with non-communicable chronic diseases. However, we have no vaccine efficiency data to reduce cardiovascular events in acute phase, and few studies have evaluated the cardioprotective potential of the influenza vaccine were conducted in countries with well-defined seasonality and/or vaccine doses not licensed in Brazil. Therefore, a study evaluating the HD vaccine in a period covering all influenza virus seasonality in Brazil can bring important findings to the different scientific gaps, as well as to clarify issues on the potential benefit of double-dose vaccine, with no contraindications, immediately after an atherothrombotic event. If a real benefit is shown, it may also be a future therapeutic tool adjuvant to traditional drug therapy for the prevention of cardiovascular events.

## **2. OBJECTIVES**

### **2.1 Primary objective**

To evaluate if increased doses of influenza vaccine at hospital phase, when compared to outpatient vaccine in the usual dose, decrease the risk of combined cardiorespiratory events (death, AMI, stroke, hospitalization for unstable angina, hospitalization for heart failure, emergency coronary revascularization or hospitalization for respiratory infection) in patients with acute coronary syndrome.

### **2.2 Secondary objectives**

The main secondary objectives aim to evaluate whether, in patients during the acute phase of an ACS, the increased dose influenza vaccine is superior to the late vaccine to prevent the following endpoints: AMI; CVA; TIA; cardiovascular death; total mortality; pulmonary death; hospitalization for unstable angina; need of coronary revascularization (emergency and non-emergency); acute myocardial injury; hospitalization for heart failure; hospitalization for upper airways and pulmonary infection, and stent thrombosis.

### **2.3 Exploratory objectives**

To determine the rate of adverse events related to double-dose vaccine; to compare the seroprotection between the two treatment arms with the occurrence of endpoints; occurrence of primary endpoint in up to 45 days after randomization.

### 3. STUDY PLANNING

#### 3.1 Design

Randomized, active-controlled, multicenter, open label, superiority, parallel groups and 1:1 allocation trial with blind evaluation of clinical endpoints and intention-to-treat analysis.

#### 3.2 Eligibility

##### 3.2.1. Eligibility Criteria for Hospitalized Subjects

Major Brazilian hospitals, both public and private (but preferably public hospitals, with outpatient care for patients at high cardiovascular risk), connected to a Basic Health Units reference network, will be included.

##### 3.2.2. Eligibility Criteria for Subjects

###### 3.2.2.1 Inclusion Criteria

- Males and females aged  $\geq 18$  years;
- Patients with acute coronary syndrome.

###### 3.2.2.2 Exclusion Criteria

- Participation in another clinical trial.
- Refusal to provide consent for the study;
- Hypersensitivity or anaphylaxis to any component of the vaccines;

- History of Guillain-Barré Syndrome 6 weeks after an influenza vaccine, previously to study inclusion;
- Have already received the influenza vaccine with the same strains used in the study (comprises trivalent or quadrivalent vaccines with the same strains of the study);
- Pregnant women;
- Breastfeeding women;
- Presenting ACS between the months of December and February;
- Hospitalization length for ACS > 7 days.

### **3.3 Randomization Method and Confidential Allocation**

The patients' randomization list will be generated considering a random function with equal allocation probability to one of the vaccine therapy groups and in relation to each investigational site. Each study vaccine group will be numbered and only the numbers will be used in the randomization, which will be performed through a randomization central electronic system of the project coordinating site at HIAE, guaranteeing the secrecy of the allocation. In special cases, where randomization problems occur, the coordinating site will contact the investigational site with the actions to be taken.

### **3.4 Masking**

This is an open-label study, where treatment allocation will be open to investigators, medical care team and patients. Clinical endpoints will be evaluated and validated by a Blind Independent Committee, where the blinding will be interrupted at

the end of the inclusion of the last patient, or for safety conditions related to the use of influenza vaccines, or for extraordinary necessity (case of an influenza pandemic) requiring changes in vaccines and their compositions.

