|                                | 
 
• Hypersensitivity or anaphylaxis to any component of the vaccine, or Guillain-Barré within up to 6 weeks after previous influenza vaccine;
 
• Have already received the influenza vaccine with the same strains used in the study;
 
• Breastfeeding women;
 
• Pregnant women;
 
• Presenting ACS between the months of December and February;
 
• Hospitalization length for ACS > 7 days.
 
                                                                                                           |
| Study Intervention      | 
Inactivated quadrivalent influenza vaccine, with 15 µg hemagglutinin per double-dose viral subtype (total 30 µg, HA), 0.5 mL per dose, IM.
 
Intervention Group: Two simultaneous administrations during hospital phase.
 
Control Group: Single-dose administration 30 days after index event.
                                                                                                                                                                                                                                                                                 |
| Follow-up               | 12 months from inclusion.                                                                                                                                                                                                                                                                                                                                                                                                                                                                                                                                                                        |
| Outcomes                | Outcome consists of cardiovascular and respiratory events (death, AMI, stroke, hospitalization for unstable angina or hospitalization for heart failure, emergency coronary revascularization or hospitalization for respiratory infections).                                                                                                                                                                                                                                                                                                                                                    |

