### 3.5 Study Procedures

After the ethics approval of the participating sites, each site will receive, and initiation visit for the training and qualification of the research team in the study procedures.

The study will start randomizations as soon as 2009 influenza vaccines are available (February/2019) and will continue until November/2020, even after the national influenza vaccine campaign for the mentioned years. Remembering that between the months of February/March 2020 a new randomization period is started, with the availability of influenza vaccine for the due year. In such a way that the project will have two patient inclusion periods:

*Period 1* – Influenza vaccine 2019 – Between the months of February and November 2019;

*Period 2* – Influenza vaccine 2020 – Between the months of February and November 2020.

*Period 3* – Influenza vaccine 2021 – Between the months of February and November 2021.

There is a possibility of the inclusion of another vaccination period, if the steering committee points a need of a higher patient inclusion depending on the number of events related to the primary endpoint.

Patients will be randomized after the signing the ICF in the specialized site (HUB) where they were cared for. Inclusion and exclusion criteria will be evaluated after the evaluation of the acute coronary syndrome, confirmed by electrocardiogram and/or cardiac enzyme tests. Randomization may be performed in up to seven days from the initial hospitalization related to the index event, ACS.

The indication or not of percutaneous coronary intervention will not prevent entering the study, with attention to the description of the vaccination in the CRF, both before or after the procedure.

As the beneficial effects of influenza vaccine seem to be connected to its administration in the **early ACS period**, the sites are recommended to give it **as soon as possible at the onset of symptoms**, but with attention to each unit and each case priorities of care. The failure to comply with this recommendation in no way prevents the inclusion of the patient, as he/she may also receive the vaccine at a time close to the hospital discharge.

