## 2. STUDY METHODS

### 2.1. Trial Design

A randomized controlled, open-label, multicenter, superiority, parallel group and 1:1 allocation trial, with blind assessment of clinical outcomes.

After evaluation of an acute coronary syndrome (ACS) confirmed by exams, and during hospitalization phase, if the patient attends to the enrollment criteria and signs the consent form, the randomization to one of the vaccination arms of the study will occur.

The patient can be randomized to one of the following arms:

- 1) Double-dose influenza vaccination (DD) – administered during the hospital stay phase, as early as possible following randomization
  - 2) Standard dose influenza vaccination (SD) – administered  $30 \pm 5$  days after randomization
- Subsequently to the randomization date, each patient will be followed for 12 months, for the monitoring of cardiovascular and respiratory events.

The study was planned to initiate the randomizations from the availability of the 2019 influenza vaccine (March 2019) and continue until November 2020, even beyond the national influenza immunization campaign period for those years. Despite the effort made to completion of the planned inclusion sample, ensuring the representativeness of both planned influenza periods, the first recruitment period was impaired due to regulatory delays in the study initiation. Since the beginning of the second recruitment period, the protocol was amended (version 4, of 04-Jul-2020), the study sample size was recalculated as an event-driven study, and the timing of final analysis was set as the date when 953 primary efficacy outcome events would have occurred, even if it was necessary to continue recruitment through the year 2021.

In 2020, the COVID-19 pandemic impacted recruitment and conduct of the trial. First of all, national influenza vaccination campaign was anticipated and the adherence to immunization was higher than before, making fewer patients eligible for the study during this recruitment period. Second, enrollment was hurdled because patients were constrained of returning to study in-person visits to receive the outpatient vaccination, should they have been assigned to the control group. Due to those issues, the study steering committee decided to end recruitment after 1,800

[figure not shown][figure not shown]

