## 2.2. Randomization

The randomization was performed through the electronic CRF, using the HIAE Data Management System, which was validated by previous studies, presenting safety and reliability for the VIP-ACS study. The randomization list of patients was generated considering a random function with equal probability of allocation to one of the vaccine therapies groups, stratified by research center, using blocks of 8, 10 and 12. Each vaccination arm was numbered and only the numbers were used in the randomization, which was done by the central electronic randomization of the project's coordinating center in the HIAE, ensuring the concealed allocation.

This is an open-label study in which researchers, health care workers and patients are aware of the treatment allocation. All clinical outcomes were evaluated and validated by an Independent Clinical Events Committee, whose members were blinded to the study arm assignments.

[figure not shown][figure not shown]

**Figure 1.** Randomization scheme and follow-up of the VIP-ACS study. ACS = acute coronary syndrome; DD = Double dose of vaccine; SD = Standard dose; V1 = visit 1; V2 = visit 2; V3 = visit 3; VS 1 = visit for safety 1; VS 2 = visit for safety 2; mo= months.

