### **5.5 Subgroup analyses:**

As many of the baseline characteristics are known to be prognostic for the clinical outcomes in the study population with high-risk cardiovascular disease (as sex, age group, race/ethnicity, smoking status, etc.), internal consistency of the primary analysis will be assessed in subgroups defined by these and other baseline characteristics.

Heterogeneity of efficacy will be assessed using interaction tests of treatment by each of these baseline covariates and by influenza season (Period), using the same aforementioned models.

The following subgroups will be prespecified in this SAP:

- Male vs. females;
- Age  $\geq$  vs. < 60 years;
- ACS presentation: (STEMI, NSTEMI, unstable angina)
- Diabetes vs. no diabetes;
- Smokers vs, non-smokers
- White race vs. non-white
- Killip class 2 or more vs. Killip class 1
- Previous heart failure vs not;
- Previous MI vs not;
- Previous stroke vs. not;
- Previous PCI vs not;
- Previous CABG vs not;
- History of chronic lung disease vs not;
- Prior COVID-19 vs.not.

[figure not shown]

- Time from presenting ACS to randomization (in tertiles)
- Time from hospitalization to randomization (in tertiles)
- Influenza season (Mar-Jul vs. other months);
- Enrollment year (2019 vs. 2020);
- Regions of the country (North and Northeastern vs others)
- COVID-19 vaccination vs not-vaccination.

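### Protocol 3.4 ends the endpoint committee's blinding at last inclusion, with up to 12 months of follow-up still to run, and contradicts the SAP and the protocol's own design text

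*Combined protocol and SAP*

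**What the plan says.** Protocol 3.4 Masking first states that "treatment allocation will be open to investigators, medical care team and patients". It then assigns the endpoints to an independent blinded committee and names the moments at which that committee stops being blinded: "the end of the inclusion of the last patient, or for safety conditions related to the use of influenza vaccines". A further trigger is exceptional need, such as an influenza pandemic that forces a change of vaccine. Since sites and patients already know the allocation, the committee's blinding is the only blinding this sentence can refer to.

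The synopsis sets follow-up at "12 months from inclusion". SAP 2.1 agrees that, from randomization, "each patient will be followed for 12 months".

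Elsewhere the documents put no end date on blinded assessment. The protocol synopsis (Study Design and Methodological Quality) and protocol 3.1 promise blind evaluation of endpoints. SAP 2.2 says: "All clinical outcomes were evaluated and validated by an Independent Clinical Events Committee, whose members were blinded to the study arm assignments". SAP 5.1 also describes the committee's review as blinded.

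**The concern.** When the last patient is included, that patient has the full 12 months ahead and others enrolled in the same season have part of it. On a literal reading of 3.4, the committee may know the arm when it judges everything reported from then on.

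Committee judgement decides what counts. Under SAP 5.1, suspected events that the committee does not confirm, or cannot classify, are not outcomes. All-cause death is the only primary tier that does not depend on such a decision. The other six do: infarction, stroke, unstable angina, heart failure hospitalization, urgent revascularization and respiratory hospitalization. Several definitions in protocol 4.4 leave real room for judgement:

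- infarction against non-ischemic injury;
- urgent against non-urgent revascularization;
- whether heart failure or infection decisively prolonged a stay.

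The key secondary outcome also needs a ruling on cardiovascular cause of death. Sites and patients are unblinded throughout, so knowledge of allocation at the adjudication step could move the result in either direction.

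**Working it through.** **The texts side by side**

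| Place | Adjudication blinded? | End of blinding stated |
|---|---|---|
| Protocol synopsis; protocol 3.1 | Yes | None |
| Protocol 3.4 | Yes | Last inclusion, safety, or extraordinary necessity |
| SAP 2.2 | Yes, all clinical outcomes, past tense | None |
| SAP 5.1 | Yes, blinded review | None |

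Protocol 3.4 stands alone. Annex B item 17 marks blinding as unchanged, so version 6 carried the sentence forward.

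**How much could fall after the trigger**

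The plan gives no figure for this, so there is none to reproduce. The calculation below only sizes the range.

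Inputs from the documents: 12 months of follow-up; control rates and reductions from protocol 6.1; independence of components and exponential event times from SAP 2.3; and the SAP 2.3 remark that cardiovascular incidence is highest in the first 45 days.

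Assumptions: entry is uniform from the start of March to the end of November in each season; the split between seasons is as shown in the table; and the share of 12-month events falling in the first 45 days (1.5 months) is either not raised (constant hazard) or q = 30% or 50%.

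*Constant hazard.* For a last-season patient, let r be the months elapsed between entry and last inclusion; r is uniform on 0 to 9. The mean share of follow-up still to come is 1 - 4.5/12 = 0.625. A February start gives 1 - 5/12 = 0.583, so the start month matters little. Patients from earlier seasons have completed 12 months by then and contribute 0. With a fraction f of patients in the last season, the overall share is 0.625 f.

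*Early-weighted hazard.* The mean of P(T > r) over r from 0 to 9 is

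[1.5 - 0.75q + (1 - q)(10.5² - 3²)/(2 × 10.5)] / 9.

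For q = 0.3 this is (1.275 + 3.375)/9 = 0.517. For q = 0.5 it is (1.125 + 2.411)/9 = 0.393. Each is multiplied by f.

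| Assumed enrolment | f | Constant | 30% by day 45 | 50% by day 45 |
|---|---|---|---|---|
| All in 2020 | 1 | 62.5% | 51.7% | 39.3% |
| 2019:2020 = 25:75 | 0.75 | 46.9% | 38.8% | 29.5% |
| 2019:2020 = 50:50 | 0.5 | 31.3% | 25.8% | 19.6% |
| 2019-2021, equal thirds | 1/3 | 20.8% | 17.2% | 13.1% |
| 2019-2021, 10:80:10 | 0.1 | 6.3% | 5.2% | 3.9% |

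A simulation with the same assumptions gives the same shares to within rounding. Two seasons give about 20-63% and three seasons about 4-21%. Adjudication follows the event. With an assumed 3-month lag, the simulated shares judged after last inclusion rise to 34-83% and 8-29%.

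*In patients.* The chance of at least one component is 1 - Π(1 - p):

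- Control: 1 - 0.93 × 0.966 × 0.99 × 0.973 × 0.971 × 0.99 × 0.99 = 0.176.
- Double dose: 1 - 0.95 × 0.975 × 0.993 × 0.981 × 0.978 × 0.992 × 0.993 = 0.131.
- Expected patients with an event: 900 × (0.1764 + 0.1307) ≈ 276.

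Applying the shares gives roughly 54 to 173 patients with two seasons (0.196 and 0.625 × 276) and 11 to 58 with three (0.039 and 0.208 × 276.5).

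**The case against.** The best defence is that blinding was probably kept. Four places describe blinded adjudication without limit. SAP 2.2, in version 2.0 of 14 March 2022, says in the past tense that all clinical outcomes were judged by blinded members. The adjudication procedure in protocol 9.5 has no unblinding step. The other triggers in 3.4, vaccine safety and a pandemic, read like code-break conditions for the whole study, so the first may be a loose translation of the end of the last patient's participation.

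Much of this stands. A reader might infer from 3.4 that late events were in fact adjudicated unblinded. The documents do not support that; they show a contradiction. The translation reading, however, is inference, since nothing in the text says it. The past tense of SAP 2.2 covers the whole of follow-up only if enrolment ended with the 2020 season. Protocol 3.5 also lists "Influenza vaccine 2021 – Between the months of February and November 2021", and patients enrolled then would still have been in follow-up in March 2022.

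A reader might also infer that a large share of events is exposed, or that the win ratio is biased by some stated amount. The first depends on the split between seasons, which is not given. The SAP points towards two seasons: 2.3 uses aggregate data from the end of the second season, and the enrolment-year subgroup in 5.5 covers 2019 and 2020 only. SAP 2.1 adds that the first season was impaired. None of this settles the split. The second would need a difference between arms in confirmation rates after unblinding, and no document offers one. Nor do all patients have a year left at the trigger: 12 months is exact only for the last.

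**Conclusion.** The contradiction is certain and rests on the text alone. Protocol 3.4 ends the committee's blinding at last inclusion, while four other places describe blinded adjudication without an end. As written, the rule is wrong for an open-label trial with judgement-based endpoints, because following it would allow unblinded adjudication. Whether it was followed is unknown, and the SAP suggests it was not.

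The size is conditional: about 20-63% of events after last inclusion with two seasons, and about 4-21% with three. These figures rest on assumed uniform entry, assumed season splits and assumed hazard shapes. They measure exposure to the rule, not bias, and no win ratio bias figure should be attached to them. All-cause death, the first tier and the one with the highest assumed rate (7.0% in control), is not exposed in the primary outcome. This is a should-fix contradiction bearing on assessment bias.

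**What to change.** Amend protocol 3.4 to say that committee members stay blinded to allocation until all 12-month events are adjudicated and the database is locked. Align SAP 2.2 and 5.1 by stating the same end point. Confirm in the trial record that this is what was done. If any event was adjudicated after unblinding, re-adjudicate it from a package with allocation redacted and report how many there were.

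The cost is one sentence in the protocol and a matching line in the SAP if blinding was kept. Re-review of a limited set of packages is needed only if it was broken.

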### 3.5 Study Procedures

After the ethics approval of the participating sites, each site will receive, and initiation visit for the training and qualification of the research team in the study procedures.

The study will start randomizations as soon as 2009 influenza vaccines are available (February/2019) and will continue until November/2020, even after the national influenza vaccine campaign for the mentioned years. Remembering that between the months of February/March 2020 a new randomization period is started, with the availability of influenza vaccine for the due year. In such a way that the project will have two patient inclusion periods:

*Period 1* – Influenza vaccine 2019 – Between the months of February and November 2019;

*Period 2* – Influenza vaccine 2020 – Between the months of February and November 2020.

*Period 3* – Influenza vaccine 2021 – Between the months of February and November 2021.

There is a possibility of the inclusion of another vaccination period, if the steering committee points a need of a higher patient inclusion depending on the number of events related to the primary endpoint.

Patients will be randomized after the signing the ICF in the specialized site (HUB) where they were cared for. Inclusion and exclusion criteria will be evaluated after the evaluation of the acute coronary syndrome, confirmed by electrocardiogram and/or cardiac enzyme tests. Randomization may be performed in up to seven days from the initial hospitalization related to the index event, ACS.

The indication or not of percutaneous coronary intervention will not prevent entering the study, with attention to the description of the vaccination in the CRF, both before or after the procedure.

As the beneficial effects of influenza vaccine seem to be connected to its administration in the **early ACS period**, the sites are recommended to give it **as soon as possible at the onset of symptoms**, but with attention to each unit and each case priorities of care. The failure to comply with this recommendation in no way prevents the inclusion of the patient, as he/she may also receive the vaccine at a time close to the hospital discharge.

Vaccine during the hospitalization for the index event will be given in two doses, divided into 0.5 mL intramuscularly in the deltoid, sequentially in each of the patient's arms; in case the vaccine cannot be given in the upper limbs, there is a possibility of giving the vaccine in the lower limbs by employing the vaccination strategy in each member.

Patients randomized to the late standard dose influenza vaccine group (0.5 mL) will receive this vaccine at the 30 days  $\pm 5$  visit (V1) after randomization. For every patient who is still hospitalized at V1, the visit and the vaccine will take place in a hospital setting.

**After the vaccine all the patients** will be evaluated on day **7(+2) and on day 28(+3)**, by interview or phone, for the evaluation of potential local and systemic adverse occurrences that might occur, i.e., to evaluate potential reactogenic/adverse effects. In case of some adverse reaction, it will be controlled by therapies for improvement, control of signs and symptoms, and subsequently described in the eCRF.

Pharmacological therapies for the treatment of ACS will be those provided for by current guidelines, as well as by the protocols standardized by each research site.

Patients must return to the proper investigators sites for follow-up visits in 30 days  $\pm 5$  days (V1), 06 months  $\pm 10$  days (V2) and 12 months  $\pm 20$  days (V3) as of the randomization date. In special cases, exceptionally, remote contact may occur for the 6

(V2) and 12 (V3) months visits. During this period, patients will also be contacted by the research teams by phone to keep the compliance with the study and to monitor potential clinical events, as described in figure 1.

Understanding the study design, the patients will be randomized in up to seven calendar days of the index event (ACS). In the randomization defines that the patient will receive the double-dose, it must be given during the hospitalization phase for this event (at any time, during hospitalization). Patients randomized to late administration of standard dose influenza vaccine will receive a single dose at the 30  $\pm$  5 days visit from randomization. The other follow-up visits will be at 06 months  $\pm$  10 days and 12 months  $\pm$  20 days from randomization. All the patients will have three visits established in the study, as in **figure 4**.

**Double-dose vaccine at the hospitalization for index event and *Late administration of standard dose vaccine at the 30-day visit after randomization:***

[figure not shown]

**Figure 4.** Description of study follow-up visits. Follow-up visits are described as V1, V2, V3. Safety visits are described in red.

**Keys:** DD = Double-dose vaccine; SD = Standard dose vaccine; SV = Safety Visit.

